## Abstract

**Background:**

Preterm birth is a major cause of neonatal mortality and morbidity. As preventive strategies are largely ineffective, threatened preterm labor is a frequent problem that affects approximately 10 % of pregnancies. In recent years, risk assessment in these women has incorporated cervical length measurement and fetal fibronectin testing, and this has improved the capacity to identify women at increased risk for delivery within 14 days. Despite these improvements, risk for preterm birth continues to be increased in women who did not deliver after an episode of threatened preterm labor, as indicated by a preterm birth rate between 30 to 60 % in this group of women. Currently no effective treatment is available. Studies on maintenance tocolysis and progesterone have shown ambiguous results. The pessary has not been evaluated in women with threatened preterm labor, however studies in asymptomatic women with a short cervix show reduced rates of preterm birth rates as well as perinatal complications.

The APOSTEL VI trial aims to assess the effectiveness of a cervical pessary in women who did not deliver within 48 h after an episode of threatened preterm labor.

**Methods/Design:**

This is a nationwide multicenter open-label randomized clinical trial. Women with a singleton or twin gestation with intact membranes, who were admitted for threatened preterm labor, at a gestational age between 24 and 34 weeks, a cervical length between 15 and 30 mm and a positive fibronectin test or a cervical length below 15 mm, who did not deliver after 48 h will be eligible for inclusion. Women will be allocated to a pessary or no intervention (usual care). Primary outcome is preterm delivery < 37 weeks. Secondary outcomes are amongst others a composite of perinatal morbidity and mortality. Sample size is based on an expected 50 % reduction of preterm birth before 37 weeks (two-sided test, α 0.05 and β 0.2). Two hundred women with a singleton pregnancy need to be randomized. Analysis will be done by intention to treat.

**Discussion:**

The APOSTEL VI trial will provide evidence whether a pessary is effective in preventing preterm birth in women who did not deliver 48 h after admission for threatened preterm labor and who remain at high risk for preterm birth.

**Trial registration:**

Trial is registered at the Dutch Trial Register: http://www.trialregister.nl, NTR4210, date of registration: October 16th 2013.

## Background

Preterm birth, defined as birth before 37 weeks gestational age, affects 5-12 % of pregnancies in the developed world [1, 2]. Since neonatal mortality and severe morbidity rates are inversely proportional with gestational age, preterm birth is held accountable for 75 % of neonatal mortality and 70 % of short and long-term neonatal morbidity [1, 2]. Despite all efforts to reduce the incidence of spontaneous preterm birth, rates remain constant making preterm birth a major challenge for obstetric healthcare professionals.

Threatened preterm labor often precedes preterm birth and is a heterogeneous clinical condition in which labor seems to start before 37 weeks gestational age [3]. It presents itself by frequent uterine contractions leading to cervical changes or by preterm prelabor rupture of the membranes (PPROM). Approximately 10 % of all pregnant women experience an episode of threatened preterm labor requiring hospital admission [4]. Cervical length and fetal fibronectin (fFN) testing are used to differentiate between women at an increased risk for preterm delivery and those who are unlikely to deliver [5, 6]. The APOSTEL-I study showed that women with a cervical length less than 15 mm or a cervical length between 15 and 30 mm and a positive fFN test result are at increased risk for preterm delivery within seven days. In addition, the risk of preterm birth in women who do not deliver within the first seven days continues to be increased (30 to 60 %) in the subsequent weeks of pregnancy [4, 5, 7–9].

Currently, women with threatened preterm labor before 34 weeks gestational age and a high predicted risk for delivery at short-term, usually defined as delivery within seven days, are treated with tocolysis and antenatal corticosteroids to improve neonatal outcome [10]. No effective treatment has been established yet for women who did not deliver, although these women still remain at an increased risk (25 %) to deliver before 34 weeks when cervical length is < 15 mm or cervical length is ≥15 and < 30 mm with a positive fFN test result, respectively [11].

The APOSTEL-II trial showed no beneficiary effect of maintenance tocolysis with nifedipine compared to placebo on a composite of adverse perinatal outcome [12].

Results on progesterone as maintenance tocolysis are contradictive. A Cochrane review found no differences in reduction of preterm birth or neonatal outcomes [13]. Whilst another recently published systematic review, including other studies, did find a significant benefit from vaginal progesterone in reduction of preterm birth and prolongation of pregnancy [14]. However, both systematic reviews did not include the largest study available on vaginal progesterone in women with preterm labor that concluded that there was no beneficiary effect [15].

Currently no RCTs have been published investigating a cervical pessary in women with threatened preterm labor. However, results in asymptomatic women with short cervical length and singleton as well as multiple pregnancies look promising, with reported reduction of poor perinatal outcome for singleton (RR 0.14 (95 % CI; 0.01 to 0.39)) and multiple pregnancies (RR 0.23 (95 % CI; 0.09 to 0.60)) [16, 17]. Additionally, in these women with a short cervical length decreased rates were found for delivery < 34 weeks in singleton pregnancies (RR 0.18 (95 % CI; 0.08 to 0.37)) and delivery < 32 weeks in multiple pregnancies (RR 0.44 (95 % CI 0.20 to 0.98)).

In conclusion, women who do not deliver after an episode of threatened preterm labor remain at increased risk of preterm birth in the subsequent weeks of pregnancy [11] and as of yet there is no effective treatment to prevent a preterm delivery in these women Therefore the objective of the APOSTEL VI trial is to investigate whether treatment with a cervical pessary is effective in reducing preterm birth in women who remain at high risk for preterm birth after an episode of threatened preterm labor, in which they did not deliver.

## Methods/Design

### Aim

The aim of the APOSTEL VI trial is to evaluate whether treatment with a cervical pessary is effective in reducing preterm birth < 37 weeks in women who have not delivered after an episode of threatened preterm labor between 24^+0^ and 34^+6^ weeks gestational age but remain at increased risk for preterm delivery.

### Participants/eligibility criteria

A woman, ≥ 18 years, becomes eligible 48 h after primary admission for threatened preterm labor and subsequent inclusion and randomization must take place within the following 72 h. Within the first 48 h of admission treatment with antenatal corticosteroids and tocolysis will be applied according to the national preterm labor guideline by the Dutch College of Obstetricians and Gynaecologists (NVOG) [10].

Women who did not deliver after a 48-h episode of threatened preterm labor will be eligible for randomization if they comply with the following criteria:

#### Inclusion criteria

o Threatened preterm labor as defined from; 
o Cervical length less than 15 mm (<15 mm)

*OR* 
o Cervical length between 15 and 30 mm (≥15 mm and < 30 mm) AND a positive fibronectin test resulto No delivery within 48 h after admission for threatened preterm laboro Singleton or twin gestationo Gestational age between 24^0/7^ and 34^6/7^ weeks with intact membranes.

#### Exclusion criteria

o Ruptured membraneso Signs of intra-uterine infection (maternal fever, tachycardia at Cardiotocography (CTG))o Signs of fetal distress at CTGo Known major fetal anomalieso Cervical dilatation ≥3 cmo >72 h elapsed after becoming eligible to participateo Residual cervical length that makes it impossible to place a pessary

A flow diagram for patient selection can be found in Fig. 1.

**Fig. 1 Fig1:**
[figure not shown]
Flowchart Apostel VI

### Procedures, recruitment, randomization and collection of data

This is a nationwide multicenter open-label randomized clinical trial in eight perinatal centers with neonatal intensive care unit (NICU) facilities in The Netherlands who collaborate in the Dutch Consortium for Healthcare Evaluation and Research in Obstetrics and Gynecology - NVOG Consortium 2.0 (www.studies-obsgyn.nl). The Dutch Obstetric Consortium is a research collaboration of obstetric clinics in the Netherlands. All centers will be responsible for identification, recruitment and randomization of eligible women.

All women admitted for threatened preterm labor will receive written study information, available in Dutch and English and will be counselled by Good Clinical Practice trained nurses, midwives or doctors. After written informed consent, eligible women will be randomized to treatment with a cervical pessary or no treatment (usual care) through a web based application hosted by the Clinical Trials Unit of the Academic Medical Center, Amsterdam, according to a computer-generated randomization sequence in a 1:1 ratio, with a random block size with a maximum of four. Randomization will be stratified by type of gestation (singleton versus twin pregnancy). Demographical, medical and obstetrical information will be collected at baseline. Baseline information will be merged with relevant information collected during participation in the study in an online case report form (CRF) by GCP trained research nurses and midwives.

### Intervention

Women allocated to a cervical pessary will receive an Arabin® pessary. This is a double ring shaped pessary made of non-allergic, soft and flexible silicone, available in different sizes. During a simple vaginal examination that is not painful, a midwife or gynaecologist will assess which size pessary fits best and subsequently the pessary is folded and placed around the cervix.

The pessary will remain in place until 36 weeks gestational age or until delivery, whatever comes first. Removal of the pessary, reason of removal and reinsertion of a new pessary will be recorded. Apart from pessary placement, all women will receive care according to local protocol.

### Outcome measures

#### Primary outcome measure

The primary outcome will be preterm birth before 37 weeks of gestational age.

#### Secondary outcome measures

Secondary outcomes will be a composite of adverse perinatal outcome, time–to-delivery, gestational age at delivery, preterm birth before 32 and 34 weeks gestational age, birth weight and percentile, days of admission in hospital, NICU admission, maternal morbidity, maternal admission days for preterm labor, re-admittance for new symptoms of preterm labor, side-effects of pessary, days on additional oxygen or supported ventilation and costs. Outcomes will be recorded up until 12 weeks corrected age.

Composite adverse perinatal outcome is defined as perinatal death or severe morbidity. This composite includes: severe respiratory distress syndrome (RDS), bronchopulmonary dysplasia (BPD) according to *Jobe and Bancalari* [18], intraventricular haemorrhage grade III or IV according *de Vries et al.* and *Ment et al.* [19, 20], necrotizing enterocolitis (NEC) > stage 1 according to *Bell et al.* [21], periventricular leucomalacia > grade 1, culture proven sepsis and death before discharge from the hospital.

### Statistical issues

#### Sample size

Based on findings of previous studies we anticipate a reduction of preterm birth < 37 weeks with 50 % [16, 17].. We need to include 180 women in total (two groups of 90 women), with an alpha error of .05 and beta error .2 to show a reduction of preterm birth < 37 weeks from 40 % to 20 %. Assuming a 10 % drop out rate we will need to randomize a total of 200 participants (100 participants per group). Primarily the aim is to include 200 women with a singleton pregnancy. Women with a twin pregnancy will be included as well, however they will not contribute to the number of required inclusions.

#### Data analysis

The analysis will be done by intention to treat. The primary analysis will be limited to singletons only; a secondary analysis will include both women with a singleton and a twin pregnancy. Differences in the main outcome preterm birth < 37 weeks’ between the pessary and no treatment group will be assessed using a random intercept, fixed effects binomial regression model with a log-link function, resulting in a relative risk (RR) with accompanying 95 % confidence interval (CI). In the secondary analysis stratified randomization by type of gestation will be accounted for by adding the type of pregnancy as a covariate to the regression model. In case of equivalence in outcomes between treatment allocations, the analysis will be repeated on a per protocol basis.

Secondary outcomes on the child level in the primary analysis and secondary outcomes on the maternal level in both the primary and secondary analysis will be analyzed equivalent to the primary outcome measure. In the secondary analysis dichotomous outcomes on the infant level will be assessed using a binomial generalized estimating equations model (GEEs) with a log-link function and using an unstructured correlation matrix, resulting in a relative risk (RR) with accompanying 95 % confidence interval (CI). We will account for interdependence between outcomes in twin pregnancies by considering the mother as a cluster variable [22]. Time to delivery will be assessed using Kaplan-Meier analysis with a log-rank test to assess the statistical significance between curves, and a Cox proportional hazards model.

Pre-specified subgroup analysis will be performed on singletons only and is planned based on risk stratification (cervical length < 15 mm versus cervical length ≥15 mm and < 30 mm and positive fetal fibronectin) and obstetric history subdivided on parity and a history of preterm birth (nulliparous versus multiparous with history of preterm birth and multiparous women without a history of preterm birth). Subgroup effects will be investigated for the outcomes preterm birth < 37 weeks and adverse perinatal outcome and will be assessed by including an interaction term between the subgrouping variable and treatment allocation as a covariate to the regression model. When the interaction shows to be statistically significant (*p <* 0.05) a stratified subgroup analysis will be performed to study the effect of treatment in different strata of the subgroup.

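### The singleton primary model is valid but names no baseline covariate; pre-specified adjustment for gestational age at entry, cervical-length group and previous preterm birth would bring a nil-to-modest gain in precision

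*Protocol article*

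**What the plan says.** The primary outcome section is brief: "The primary outcome will be preterm birth before 37 weeks of gestational age". Under Data analysis, the primary analysis is by intention to treat in singletons, and the between-group difference "will be assessed using a random intercept, fixed effects binomial regression model with a log-link function", giving an RR with 95 % CI. The unit of the random intercept is not named. Type of pregnancy is the only adjustment covariate mentioned. It belongs to the secondary analysis of singletons and twins together, where it reflects the only randomisation stratum.

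The same section uses cervical-length risk group and obstetric history (parity combined with previous preterm birth) as pre-specified subgroup variables in singletons, tested by an interaction with treatment. Gestational age at entry is an eligibility item (24+0 to 34+6 weeks) but has no role in the analysis.

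On data, the Procedures section says: "Demographical, medical and obstetrical information will be collected at baseline". The Background describes "women with a cervical length less than 15 mm or a cervical length between 15 and 30 mm and a positive fFN test result" as being at increased risk of early delivery, without separating the two groups.

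**The concern.** Plurality is constant in a singleton analysis, so the stratified randomisation balances nothing there. Gestational age at entry, cervical-length group and previous preterm birth are balanced by chance alone in about 200 women.

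Gestational age at entry also helps to set the outcome window. A woman entering at 24+0 weeks has 13 weeks at risk before 37+0; one entering at 34+6 has 2 weeks and 1 day. A variable that changes the exposure time about sixfold (91 days against 15) is a natural covariate.

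Two things are at stake. One is precision that could be had from data already collected. The other is having a covariate set fixed in advance, so that a baseline imbalance in this open-label trial does not prompt a choice of adjustment after the results are seen.

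**Working it through.** **1. Does the design depend on adjustment?** Inputs from Sample size and the Abstract: a trial "to show a reduction of preterm birth < 37 weeks from 40 % to 20" per cent, "with an alpha error of .05 and beta error .2", "two-sided test, α 0.05 and β 0.2". With p1 = 0.4, p2 = 0.2, mean 0.3 and d = 0.2:

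- Uncorrected n per arm = [1.96·√(2·0.3·0.7) + 0.842·√(0.4·0.6 + 0.2·0.8)]² / 0.2² = (1.270 + 0.532)² / 0.04 ≈ 81.2, so 82 per arm (164 in total).
- With continuity correction: (81.2/4)·[1 + √(1 + 4/(81.2·0.2))]² ≈ 91 per arm (182 in total).
- The plan says "We need to include 180 women in total (two groups of 90 women"). The corrected formula reproduces this to within two women, and 180/0.9 = 200 randomised.
- Power without continuity correction, at 90 per arm: Φ[(0.2·√90 − 1.270)/0.632] = 83.9 %. At 100 per arm: 87.6 %.

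The sample size is an unadjusted calculation, and 80 % power is met without covariates.

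**2. How strong are the covariates?** The documents do not say. The Background gives one risk, 25 % before 34 weeks, for both cervical-length groups and no rate by gestational age at entry. Prognostic strength therefore has to be assumed and shown as a range.

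**3. What does adjustment gain?** Simulation with 90 per arm, 40 % against 20 %, 4,000 trials per setting and no centre effect. The covariates are a risk group with assumed 50 % prevalence and a standardised gestational age. Power and type I error come from logistic models. The variance ratio (adjusted over unadjusted) is for the standardised log RR.

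| Assumed OR: risk group / per SD of gestational age | Power, unadjusted | Power, adjusted | Type I error, unadjusted | Variance ratio |
|---|---|---|---|---|
| 1 / 1 | 83.2 % | 83.5 % | 5.25 % | 1.01 |
| 1.5 / 1.25 | 84.3 % | 85.0 % | 5.05 % | 0.99 |
| 2 / 1.5 | 84.7 % | 86.4 % | 4.65 % | 0.97 |
| 3 / 2 | 83.6 % | 88.5 % | 4.90 % | 0.90 |

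The Monte Carlo standard error of a power figure is about √(0.84·0.16/4000) = 0.6 points, so the first row shows no real gain. In the last row the mean log RR is −0.709 unadjusted and −0.708 adjusted, so adjustment does not move the target. A variance ratio of 0.90 is worth 180/0.90 = 200 women analysed without adjustment, about 20 more than the 180.

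Two other simulations agree in scale. Log-link Poisson with robust variance at 90 per arm gave variance ratios of 1.02 (no prognostic value), 0.95 (moderate) and 0.89 (strong), with 0 to 6 points of power. Simulations of 200 women, some of which also adjusted for previous preterm birth, gave a 1 to 5 % lower variance and 0 to 3 points of power.

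**4. How much could chance imbalance matter?** Assume half the women are in each cervical-length group and 100 per arm. The chance of a difference of 10 points or more in group share is 2·[1 − Φ(0.10/√(2·0.25/100))] = 2·[1 − Φ(1.414)] = 0.157. If the groups differ by 20 points in risk (assumed), a 10-point imbalance moves the arm difference by 0.10·20 = 2 points. The standard error of that difference is √(0.24/100 + 0.16/100) = 6.3 points, so the shift is about 0.3 standard errors.

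**The case against.** The strongest reply is that the stated analysis needs no repair. An unadjusted randomised comparison is unbiased, its confidence interval already allows for chance imbalance, and the simulated type I error stays at about 5 %. This stands in full. A reader might infer from the missing covariates that the primary RR is biased or the trial underpowered; the documents support neither.

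A second reply is that a condensed article may leave its covariate list to a full protocol or SAP that is not shown. This stands to the extent that the absence is not an error. It does not dispose of the suggestion, because the section sets out the singleton model in detail and says in which analysis a covariate enters.

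Third, a reader might say that the plan ignores cervical length and obstetric history. It does not: both are pre-specified subgroup variables for the primary outcome. What remains is that an interaction analysis leaves the primary RR unadjusted, and that gestational age at entry appears in neither place.

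Fourth, it is tempting to say that the log-binomial model will fail to converge. As written it names no continuous covariate, so that risk arises only once gestational age is added, and any proposal to adjust must deal with it.

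Finally, simply swapping in a Poisson model would drop the planned random intercept in a trial run in eight centres. That is a fair criticism, and the fix below has to meet it.

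**Conclusion.** The point holds as an optional improvement. The singleton primary analysis is valid as written, but it names none of three baseline factors that are already collected, plausibly prognostic and left unbalanced by the plurality strata.

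The expected gain is nil to modest: about 0 to 10 % off the variance of log RR and about 0 to 5 points of power, with the strongest setting of one simulation slightly above that. The downside is a somewhat more complex model and a variance increase of about 1 to 2 % if the covariates are not prognostic.

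These sizes rest on assumed odds ratios, an assumed 50 % risk-group prevalence and simulations without centre effects, so they are indicative only. That gestational age at entry is prognostic is an inference from the time at risk, not a figure in the documents.

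**What to change.** Before any outcome data are seen by arm, state in the analysis plan that the singleton primary model includes treatment, gestational age at randomisation, cervical-length group (below 15 mm, or 15 to below 30 mm with positive fibronectin) and previous preterm birth as fixed covariates.

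- Keep the RR with 95 % CI as the effect measure.
- Name the unit of the random intercept, and keep that intercept or an equivalent way of handling the same clustering.
- Use log-link Poisson regression with robust variance, either as the primary model or as the stated fallback if the log-binomial model does not converge.
- State the functional form of gestational age in advance. Linear is the simplest choice, but the documents do not establish it.
- Report the unadjusted RR as a sensitivity analysis.

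The cost is wording in the analysis plan. Two covariates are eligibility items and the third is needed for the planned subgroup analysis, so no new data are collected and the sample size is unchanged.

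### The per-protocol analysis is triggered only by an undefined equivalence finding, which in this superiority trial can in practice mean only a non-significant intention-to-treat result

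*Protocol article*

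**What the plan says.** The Aim section sets a superiority question: to "evaluate whether treatment with a cervical pessary is effective in reducing preterm birth < 37 weeks". The abstract gives the error rates as "two-sided test, α 0.05 and β 0.2", and the Sample size section powers the trial "to show a reduction of preterm birth < 37 weeks from 40 % to 20" per cent, with 90 women per group, raised to 100 per group for drop-out.

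The Data analysis section states "The analysis will be done by intention to treat" and "The primary analysis will be limited to singletons only". The effect measure is a relative risk with a 95% confidence interval. It then adds: "In case of equivalence in outcomes between treatment allocations, the analysis will be repeated on a per protocol basis".

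The article gives no equivalence margin, no equivalence test and no power for equivalence. It plans no per-protocol analysis if ITT shows a difference. It does not say that a per-protocol result would replace the ITT result.

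On adherence, the Intervention section says: "Removal of the pessary, reason of removal and reinsertion of a new pessary will be recorded".

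**The concern.** Two things are wrong with the rule as fixed in the text.

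First, the trigger uses a term that the design cannot deliver. A two-sided superiority test ends in a significant or a non-significant difference. Without a margin, the only result that can set off the per-protocol repeat is the non-significant one. Calling that result equivalence misdescribes it.

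Second, whether the extra analysis is done depends on the primary result. It is run after a null ITT result and not after a positive one, so it can soften a null finding but never test a positive one. The extra analysis is also not protected by randomisation. The comparator is usual care, so non-placement and early removal arise mainly in the pessary arm, after allocation, in an open-label trial. If the women dropped differ in risk from those kept, the comparison is distorted.

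At stake is how a null result would be read and reported. The primary test itself is not affected.

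**Working it through.** **Inputs from the protocol article.** Control risk 40%, pessary risk 20%, two-sided alpha 0.05, power 80%, 90 evaluable and 100 randomised per group. **Assumed, not in the article:** the fraction *r* of the pessary arm excluded per protocol and the risk *q* of the excluded women.

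**1. The plan's own figure.** The pooled normal formula for 40% against 20% gives 81.2, so 82 per arm (164 in total). With continuity correction it gives 90.9, so 91 per arm (182), which agrees with the stated 180 to within 2 women. Then 180/0.9 = 200. The sizing is a superiority calculation throughout; nothing in it serves equivalence.

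**2. What a null result would show.** With 40% in both arms, SE(log RR) = sqrt(2 × 0.6/(n × 0.4)).
- n = 100: SE = 0.173; 95% CI = exp(±1.96 × 0.173) = 0.71 to 1.40. Risk difference ±1.96 × sqrt(2 × 0.24/100) = ±13.6 points.
- n = 90: SE = 0.183; 95% CI 0.70 to 1.43; risk difference ±14.3 points.

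An observed 27/100 against 40/100 (RR 0.675) would also set off the rule: z = 0.13/sqrt(0.335 × 0.665 × 0.02) = 1.95, just short of 1.96.

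For a true 30% against 40% (RR 0.75) with 100 per arm, power is Φ[(0.10 − 1.96 × sqrt(2 × 0.35 × 0.65/100))/sqrt((0.24 + 0.21)/100)] = Φ(−0.48) = 0.32. A real 25% relative reduction would therefore give a non-significant result about 68% of the time.

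**3. What one-sided exclusion does under no true effect.** With overall risk 40% in both arms, the per-protocol risk in the pessary arm is (0.40 − r × q)/(1 − r), compared with 0.40 in controls. For r = 10% and q = 30% it is 0.37/0.90 = 0.411, RR 1.03. For r = 10% and q = 70% it is 0.33/0.90 = 0.367, RR 0.92.

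The last column below is the chance of a significant benefit in ITT, or in per protocol after a null ITT. It comes from 400,000 simulated trials per row, with 100 per arm and a Wald test on log RR at 1.96. ITT alone gives 2.5%.

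| Excluded (r) | Risk of excluded (q) | Per-protocol RR | False benefit, if per protocol is read as efficacy |
|---|---|---|---|
| 10% | 30% | 1.03 | 2.6% |
| 10% | 40% | 1.00 | 2.9% |
| 10% | 50% | 0.97 | about 3.5% |
| 10% | 60% | 0.94 | about 4.7% |
| 10% | 70% | 0.92 | about 6% |
| 15% | 70% | 0.87 | about 10% |
| 20% | 80% | 0.75 | about 26% |

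The last two rows are extreme settings, included to show how steeply the figure depends on the assumptions. The simulation uses a simple two-group test and ignores the planned random intercept and the interim look.

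**The case against.** The strongest reply is that ITT is the stated basis, the sample size serves it, and the article says only that the analysis will be repeated. A reader might infer that the rule gives the trial a second route to a benefit claim and so inflates its type I error. The documents do not support that: no sentence makes the per-protocol result confirmatory or lets it override ITT. If the conclusion rests on ITT, the rule adds no type I error. The last column of the table is conditional on a misreading, and the present wording does nothing to prevent it.

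A reader might also infer that the per-protocol estimate must favour the pessary, because deviations can occur only in that arm. That is too strong. In an open-label trial a control woman could receive a pessary, and eligibility violations can occur in either arm. The article provides for reinsertion and for the pessary staying in until delivery, so a removal need not be a deviation. The per-protocol set is not defined in the article, which may properly be left to the full protocol. Nothing in the article says that women with early removal are at higher risk; if they are at lower risk, the bias reverses.

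Finally, a reader might infer that the trial intends to claim equivalence. The word appears as a trigger for an analysis, not as a planned conclusion, and the RR will be reported with its confidence interval, so the width would be visible.

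These points limit the consequences and lower the severity. They do not rescue the trigger, which remains undefined and dependent on the result.

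**Conclusion.** The point holds as a should-fix. The article itself fixes a results-dependent trigger in terms that a superiority design without a margin cannot support, so this is more than a detail left to an unseen analysis plan. Reading the trigger as non-significance is an inference, but it is the only outcome that the described tests can supply. At the planned size such a result is compatible with an RR of about 0.71 to 1.40, assuming 40% in both arms of 100.

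The per-protocol look is selective, and bias is plausible in either direction. With 10% of the pessary arm excluded at an assumed 30% to 70% risk, the RR under no effect moves between about 1.03 and 0.92. The matching false-benefit rate of about 2.6% to 6% applies only if a positive per-protocol result is taken as evidence of efficacy, which the article does not say. The primary analysis, its error rate and the sample size stand.

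**What to change.** In the Data analysis section:

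- Delete the condition and the word *equivalence*. If the term is to stay, define it with a margin and a confidence-interval rule.
- State that the conclusion rests on the ITT analysis alone and that a non-significant difference will not be described as equivalence.
- Report the per-protocol analysis whatever the ITT result, labelled as supportive and subject to selection bias from exclusions after randomisation.
- Optionally, add a complier-average effect with randomised allocation as the instrument. This is a preference; the first three changes are sufficient.

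The cost is a few sentences, plus one extra supportive analysis when ITT is positive. Pessary removal, its reason and reinsertion are already to be recorded, and the sample size stays at 180 evaluable and 200 randomised.
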